#### Design:

[figure not shown]

Participants will enter a screening period, which includes Visit 1 and if necessary a medication washout period.

Subjects who are deemed eligible after this screening period will return for a baseline evaluation (Visit 2), including clinical evaluation and mucosal specimen collection, as well as the Baseline Behavioral Questionnaire (BBQ). The BBQ will be administered by Computer Assisted Self-Interview (CASI). Subjects may complete the web-based CASI in the privacy of their own home. If a subject does not have access to the Internet, prefers to complete the BBQ at the study site, or requires assistance in using the CASI, he or she will be accommodated at the study site.

After completing Visits 1 and 2, eligible subjects will be randomized to one of three groups: 0.1% UC-781 gel, 0.25% UC-781 gel, or a placebo gel (12 per group). A subset of 9 subjects (3 from each group) will also participate in a pK sub-study, which will include 6 timepoints (Visit 3-pre, 0.25 hr, 2 hr, 4 hr, Visit 3A- 24 hr, and Visit 5- 1 day post-QD dose). During randomization, study staff will be notified if the participant is randomized to the pK substudy.

This study will involve 2 stages of treatment. **Each treatment stage is independent of the other. This study aims to examine the effects of 2 different dosing regimens, NOT cumulative safety over the both stages.**

Once randomized, subjects will return to the clinic (Visit 3), where a single dose of the study gel (Treatment Stage 1) will be administered after a preparatory Normosol-R pH7.4 enema. Within approximately 30 minutes, lavage, stool, sponge, and colorectal biopsy specimens will be obtained. Subjects will receive a safety follow-up phone call.

Subjects will return to the clinic for Treatment Stage 2 Clearance (Visit 4), in the week prior to beginning Treatment Stage 2. If given clearance, the subject may begin Treatment Stage 2.

In Treatment Stage 2, subjects will begin to self-administer once daily outpatient doses of the study gel for 7 days. Subjects will receive a follow-up safety phone call mid-way through

Stage 2. After completion of Stage 2 the subject will complete a Product Acceptability Questionnaire (PAQ) by CASI and return to clinic for evaluation and specimen collection (Visit 5). Subjects will receive a safety follow-up phone call.

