### 2.1.2 Secondary Objective

To determine whether use of study product is associated with rectal mucosal damage characterized by the following:

Parameters to be studied include:

- Epithelial Sloughing

Rationale: The sloughing assay is integral to the evaluation of microbicides in the rectum. The only microbicide previously studied in the rectum, is N-9, which led to rapid exfoliation of the rectal epithelium in mice and variable abnormality in humans. A recent study has demonstrated that up to 41% of men who have sex with men (MSM) use vaginal products containing spermicides for lubrication during rectal sex. It is important to have confidence that any microbicide going to market will not have a similar effect.

Using the N-9 example, it is expected that evidence of any injury may be apparent within 15 minutes of exposure to an offending agent. In the case of N-9, substantial reconstitution of these changes occurred by 2 hours and microscopically normal

epithelium was noted after 24 hours. The observation of epithelial sloughing was made by performing a rectal lavage and examining the effluent for epithelial cells. Measurements were conducted using either microscopy, looking for sheets of epithelia, or by counting the cells with a Coulter Counter.

Given the above information, it is best to obtain lavage specimens within the 15 minute –2 hour window after application of a product rectally. Therefore, in this study the first treatment stage will include rectal lavage in order to monitor subjects for epithelial sloughing. Although presence of some epithelial cells in effluent is normal, a dramatic increase from baseline would be concerning. In order to avoid the confounding effects of the standard pre-sigmoidoscopy prep (a hypertonic enema), a Normosol-R pH7.4 (See Appendix XI for package insert) enema will be used instead. Rectal lavage will be performed during the endoscopy at approximately 5 cm. Careful attention will be paid to perform the second lavage at 5 cm to decrease the likelihood of washing the UC-781 off of the mucosa at biopsy sites further up the colon and avoid confounding results caused by a the small amount of KY-like lubricant routinely used during the endoscopy procedure.

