### 5.3.2 Clinical Procedures

**NOTE: During this visit the timepoints listed below are approximate. Every effort will be made to adhere to the timeline, however due to logistics timing will not be exact. However, the sequence of sample collection during the following visits is crucial.**

- ⊙ Interval medical history\*, including AE assessment, will be collected to assure continued healthy status and safety of study interventions.
 

*\* Note for female participants this includes notation of the LMP.*
- ⊙ Basic physical examination as defined in section 5.1.2
 

*(If participant has peri-anal or rectal HSV lesions, referrals for treatment will be provided and Visit 3 will be postponed until outbreak resolved.)*
- ⊙ **If female of child-bearing potential, collect urine for STAT HCG testing**
- ⊙ Collect blood specimens, including pre-dose pK draw if applicable
- ⊙ Collect rectal swabs and sponge specimens

- ⊙ Administer preparatory Normosol-R pH7.4 enema
- ⊙ Collect stool specimen
- ⊙ T=0 Administration of single-dose of study gel by study staff  

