### 5.3.3 Laboratory Procedures

- ⊙ Safety labs as defined in section 5.1.3
- ⊙ STD screen as defined in section 5.1.3
- ⊙ Research panel
  - Epithelial sloughing assay (Lavage)
  - Histopathology (~1 biopsy)
  - Mucosal mononuclear cell phenotype (~4 biopsies)
  - Mucosal cytokine profile (~3 biopsies)
  - Pre- and post-dose Immunoglobulin assay (~4 rectal sponges)
  - Fecal calprotectin assay (Stool)
  - Explants studies (~6 biopsies, ~10ml blood)
  - UC-781 blood level for sub-study participants (~25ml blood)

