## 5.7 Visit 5 – (Week 6 +/- 2 weeks) Treatment 2 Follow-up

*Although time from Week 0 may vary by several weeks, visit must be scheduled for Day 8 of Treatment Stage 2 (the day following the last dose of study product +/- 1 day).*

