## **7.6 Statistical Procedures for Analysis of Mucosal Damage Parameters**

The associations of six sets of mucosal parameters with the use of study product will be examined as a secondary objective. Four of these parameter sets (Histopathology, Cell Phenotype, Cytokine profile, Fecal Calprotectin) are collected three times per patient: at baseline, post-Treatment 1 and post-Treatment 2. The remaining two sets (Epithelial Sloughing and Immunoglobulins) are four times per patient: at baseline, pre- and post-Treatment 1, and post-Treatment 2. For all six parameter panels, the main question of interest is whether the three treatment groups (placebo, low, and high) have systematically different mucosal damage parameters post-Treatment 1 and post-Treatment 2. In particular, we will be assessing whether either of the UC-781 treatment groups have evidence of more mucosal damage than the placebo group. As described below, at least four of the six parameter sets should be stable and sensitive enough that important clinical differences would be statistically detectable.

As subjects will be randomized to the three treatment groups, systematic baseline differences are not expected; however, due to the relatively small study size, it is quite likely that many parameters will be quite different between treatment groups at baseline. All analyses will therefore be conducted both with and without controlling for baseline measurements. For continuous measures, it is well-known that controlling for baseline differences in regression models is more powerful than analyzing changes from baseline.

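### Followed as written, the Visit 3 procedure list makes Section 7.6's post-Treatment 1 calprotectin a pre-dose value; 7.6 also counts a pre-dose lavage that Section 5 does not schedule

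*Protocol*

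**What the plan says.** **Analysis.** Section 7.6 (Protocol) groups the mucosal panels by sampling times. Of the first four it says "Histopathology, Cell Phenotype, Cytokine profile, Fecal Calprotectin) are collected three times per patient: at baseline, post-Treatment 1 and post-Treatment 2", and of the others "The remaining two sets (Epithelial Sloughing and Immunoglobulins) are four times per patient: at baseline, pre- and post-Treatment 1, and post-Treatment 2". The basic model is an ANCOVA of the post-Treatment 1 or post-Treatment 2 value on baseline and treatment group. Binary and ordinal measures get the logistic counterpart.

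**Visit 3 procedures.** Section 5.3.2 warns that clock times are approximate but that the order of sampling is crucial. After the enema it lists "Collect stool specimen", and next "T=0 Administration of single-dose of study gel by study staff". No later stool is listed. The only lavage belongs to the sigmoidoscopy at T=30 min. In Section 5.3.3 only one assay is split around the dose: "Pre- and post-dose Immunoglobulin assay (~4 rectal sponges)".

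**Passages that disagree.** The Schema says of the period after the gel: "Within approximately 30 minutes, lavage, stool, sponge, and colorectal biopsy specimens will be obtained". The calprotectin rationale in Section 2.1.2 has stool taken when the lavage is done, which at Visit 3 is after the gel. Section 2.2 repeats the Schema sentence but leaves stool out. The sloughing rationale in Section 2.1.2 refers to a second lavage, without saying when the first takes place.

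**The concern.** A sample taken before the gel cannot reflect the gel. If site staff follow the Visit 3 list, the calprotectin value labelled post-Treatment 1 is a second baseline. Comparing arms on it tests only whether randomisation produced similar groups. Section 7.6 expects this marker to be particularly useful for detecting mucosal damage, so an empty single-dose comparison could be mistaken for evidence of no inflammation. It would also take a place in the set of p-values that Section 7.6 adjusts by stepdown methods.

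The sloughing discrepancy is smaller. Section 7.6 counts a pre-Treatment 1 measurement for which Section 5 lists no specimen.

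**Working it through.** The protocol gives no power, effect size or intrasubject correlation for calprotectin, so it has no figure of its own to reproduce here.

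**Step 1. Time points in Section 7.6 against specimens in Section 5** (Sections 5.2.2, 5.3.2, 5.3.3 and 5.7.2)

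| Panel | Points in 7.6 | Specimens scheduled | Result |
|---|---|---|---|
| Histopathology, phenotype, cytokines | 3 | Biopsies at Visit 2, Visit 3 (T=30 min), Visit 5 | 3 of 3 agree |
| Immunoglobulins | 4 | Sponges at Visit 2, Visit 3 before and after gel, Visit 5 | 4 of 4 agree |
| Sloughing | 4 | Lavage at Visit 2, Visit 3 (T=30 min), Visit 5 | 3 of 4; no pre-dose lavage |
| Calprotectin | 3 | Stool at Visit 2, Visit 3 (before T=0), Visit 5 | Two pre-gel values, one post-Treatment 2, no post-Treatment 1 |

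**Step 2. What the calprotectin test can show if the stool is pre-dose.** The model is Y(Visit 3) = a + b·Y(Visit 2) + g(low) + g(high) + error, with 36 subjects, 4 parameters and 36 − 4 = 32 residual degrees of freedom. Both Y values precede exposure, so randomisation makes g(low) = g(high) = 0 whatever the gel does. The rejection rate is therefore the significance level, 0.05.

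A simulation of this ANCOVA checked the size of the test. It used 12 per arm, high dose against placebo, two-sided 0.05 without multiplicity correction, and 4,000 runs per setting. The two-sided level, Normal outcomes and complete data are assumptions.

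| Assumed effect (SD) | Assumed baseline correlation | Rejection, stool post-dose | Rejection, stool pre-dose |
|---|---|---|---|
| 1.0 | 0.3 | 69% | 5.0% |
| 1.0 | 0.5 | 77% | 5.2% |
| 1.0 | 0.8 | 98% | 4.8% |
| 1.5 | 0.3 | 96% | 4.2% |
| 1.5 | 0.5 | 98% | 5.0% |
| 1.5 | 0.8 | about 100% | 4.4% |

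The effects and correlations are illustrative. The last column does not depend on them beyond simulation error.

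**Step 3. Value of the Visit 3 stool as a second baseline.** Assume one common correlation r among Visits 2, 3 and 5. As a fraction of outcome variance, the residual for the Visit 5 model is 1 − r² with one baseline and 1 − 2r²/(1 + r) with the mean of two.

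- r = 0.3: 0.910 falls to 0.862, a cut of 5%
- r = 0.5: 0.750 falls to 0.667, a cut of 11%
- r = 0.7: 0.510 falls to 0.424, a cut of 17%

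These correlations are also assumed. Moreover, 14 + 14 = 28 biopsies are taken at Visit 2, between the two stool samples, so equal correlation is not assured.

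**Step 4. Timing of the lavages.** Section 2.1.2 says "it is best to obtain lavage specimens within the 15 minute –2 hour window after application of a product rectally". The Visit 3 lavage at about 30 minutes lies inside that window. For Visit 5, "visit must be scheduled for Day 8 of Treatment Stage 2", which Section 5.7 defines as the day after the last dose, give or take a day. Nominally that is about 24 hours, the point by which the nonoxynol-9 example in Section 2.1.2 describes microscopically normal epithelium.

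**The case against.** The strongest reply is that pre-dose collection is not settled. A reader of Section 5.3.2 alone might conclude that the stool is definitely taken before the gel, but the Schema and the calprotectin rationale both point the other way. The enema, stool, sigmoidoscopy order also appears at Visits 2 and 5, where no dose intervenes, so the Visit 3 list may simply carry that order over. Appendix I, the visit schedule, is not in the text at hand and may bear on this. This objection stands: the finding is a contradiction, and the 5% figure holds only if the Visit 3 list governs.

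A reader might also infer that the single-dose sloughing analysis fails. It does not. The basic models use baseline and post-treatment values, and Section 7.6 uses the baseline measurement to screen out post-Treatment 1 false positives. A Visit 2 lavage is scheduled for that purpose. Only a fourth point for exploratory longitudinal models is lost, and Section 7.6 expects little extra from those models.

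A third tempting inference is that the Visit 5 lavage is uninformative and should leave the tested set. Section 2.1.2 calls the early window best, not mandatory, and on that basis assigns lavage to the first treatment stage. Whether sloughing persists after seven daily doses is a legitimate question, and nothing in Section 7.6 claims that Visit 5 establishes acute safety. Nor does any passage commit the sponsor to reporting a null as absence of inflammation.

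Finally, these assays are secondary. Section 1.1 says they are not safety indices, and the primary adverse-event and acceptability analyses are untouched.

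**Conclusion.** The point holds as a contradiction with a conditional consequence. If Section 5.3.2 is followed, one of the two calprotectin group comparisons has a rejection rate of about 5% for any effect of the gel, and its null result carries no information on single-dose inflammation. If the stool is in fact taken after the gel, the comparison stands and the procedure list is what is wrong. The Visit 5 calprotectin comparison is sound either way.

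For sloughing, Section 7.6 overstates the time points by one relative to Section 5, and the second lavage in Section 2.1.2 has no listed pre-dose counterpart at Visit 3. The post-Treatment 1 sloughing comparison remains valid. The Visit 5 lavage bears on persistent rather than acute sloughing.

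The 5% result rests only on randomisation and pre-exposure sampling. The 5–17% variance gain rests on assumed equal correlations of 0.3 to 0.7, which the protocol does not give for calprotectin.

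**What to change.** Reconcile the Schema, Section 2.1.2 (sloughing and calprotectin rationales), Sections 5.3.2 and 5.3.3, and Section 7.6, and check Appendix I against them. Label each value by its true timing before unblinding.

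- **If the Visit 3 stool is pre-dose:** delete the post-Treatment 1 calprotectin test from Section 7.6 and treat the value as a second baseline. Averaging it with Visit 2 as the covariate for Visit 5 is optional.
- **If it is post-dose:** correct the order in Section 5.3.2; the Section 7.6 analysis then stands.
- **Sloughing:** state three time points with Visit 2 as baseline, unless a pre-dose Visit 3 lavage is in fact scheduled, in which case list it in Section 5.3.2.
- **Visit 5 lavage:** keep it in the analysis, with a sentence saying that it is interpreted as persistent rather than acute sloughing.

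The cost is wording. No new specimens are needed, and at most one test, uninformative in that case, is given up.

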### 5.2.3 Laboratory Procedures

- ⊙ Safety labs as defined in section 5.1.3
- ⊙ STD screen as defined in section 5.1.3
- ⊙ Research panel
  - Epithelial sloughing assay (Lavage)
  - Histopathology (~1 biopsy)
  - Microflora (~1 rectal swab)
  - Mucosal mononuclear cell phenotype (~4 biopsies)
  - Mucosal cytokine profile (~3 biopsies)
  - Immunoglobulin assay (~2 rectal sponges)
  - Fecal calprotectin assay (Stool)
  - Explants studies (~6 biopsies, ~10ml blood)

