The basic model for analyzing continuous measures adjusting for baseline differences will be the analysis of covariance (ANCOVA) model regressing the continuous parameter at either post-Treatment 1 or post-Treatment 2 on the continuous baseline value and the categorical treatment group membership (with placebo as the reference group). The estimated regression coefficients for the treatment group will then be directly interpretable as the difference between low vs. placebo and high vs. placebo, post-Treatment 1 or post-Treatment 2 after adjusting for baseline differences. This model without the baseline values reduces to the simple one-way ANOVA model with treatment group as the predictor. For analyzing binary or ordinal measures, we will use the logistic regression version of these models. That is, we will regress the outcome post-Treatment 1 or post-Treatment 2 on group membership and on baseline value (when adjusting for baseline differences).

As we will be analyzing group differences in a large number of parameters, some attempt must be made to account for multiple hypothesis testing. We will address this multiple comparisons problem both informally and formally. Informally, particular group differences significant at the 0.05 level or smaller will be flagged as at least suggestive and those with extremely strong p-values (e.g. 0.001 or less) will be carefully examined. In addition, differences seen consistently for related parameters will carry more weight. Formally, we will apply corrections to the p-values. Of these, the Bonferroni method is the simplest, but also the weakest. We will employ the more powerful stepdown methods implemented in

the MULTTEST procedure in SAS v 9.1 (SAS Institute, Cary, NC).

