We will also investigate longitudinal (three or four time points) and/or multivariate (simultaneous examination of multiple measures in a set) modeling techniques. The longitudinal analyses will most likely not be additionally informative, as there are only three time points for most of the parameters. Multivariate techniques are expected to result in potentially substantial power increases. Our previous studies with phenotype and cytokine panels have shown strong correlations between measures as well as good stability over time (i.e. high intrasubject correlations) in steady state for many of the measures. In this setting, for example, factors derived using principal components analysis would likely have stronger association with group membership than any one particular measure in the set. An additional strength of the longitudinal and multivariate approaches is that they provide an alternative solution to the multiple testing problem that arises with examining each timepoint and each parameter individually.

- Epithelial Sloughing

The simplest analysis for the epithelial sloughing measurements will look at the presence or absence of sloughing. Additionally, we may employ the five point ordinal scale of, which ranges from 0 (no evidence of sloughing) up to 4 (evidence in all four quadrants). For these data, there is baseline measurement will allow screening out of post-Treatment 1 false positives.

- Histopathology

As in the sloughing data, we will begin by examination of a two point (normal versus abnormal) or three point (normal, slightly abnormal, abnormal) scales. Based on initial analyses of the HPTN 056 histopathology panel data, we do not expect that quantitative measures will be substantially more informative than simple qualitative readings.

- Mucosal mononuclear cell phenotype

Many of the flow cytometry measurements from the HPTN 056 study are quite stable across time. Parameters with high intrasubject correlations (RFI measures are log-transformed) include %CD3, %CD4, %CD8, %CD31, CD38RFI on CD4+, CD38RFI on CD8+, %CD38|CD4, and %CD38|CD8 which have intrasubject correlations of between 0.7 and 0.9. Thus, we expect that clinically important differences in these parameters between treatment groups would be found to be statistically significant in our analyses. CCR5-related parameters had moderate stability (intrasubject correlations of around 0.5).

- Mucosal cytokine Profile

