The cytokine data in HPTN 056 and earlier work of our group for RANTES, IFN- $\gamma$ , and IL-10 all showed strong stability (intrasubject correlations between 0.7 or 0.8; analysis is on log-transformed scale for all three of these). Again, this suggests that any clinically meaningful differences between treatment groups are likely to result in small p-values.

- Mucosal immunoglobulins

The immunoglobulin data collected in HPTN 056 appears to be moderately stable within subject (intrasubject correlations are between 0.3 and 0.5 for various measures of IgA and IgG).

- Fecal calprotectin

The fecal calprotectin marker has been shown to be extremely sensitive for discriminating several clinical conditions such as active and inactive Crohn's disease. The large majority of measurements for inactive subjects were below normal thresholds and nearly all measurements for active subjects were above normal thresholds. For our study, this suggests that this marker will be particularly helpful in detecting evidence of mucosal damage in the treatment groups.

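### The immunoglobulin ANCOVA in Section 7.6 adjusts for one baseline value although two pre-gel values are collected; using their mean gives a modest precision gain at no cost in samples

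*Protocol*

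**What the plan says.** Section 7.6 states that epithelial sloughing and immunoglobulins are collected "four times per patient: at baseline, pre- and post-Treatment 1, and post-Treatment 2". Baseline and pre-Treatment 1 are therefore separate samples. The Schema fixes the baseline at Visit 2: participants "will return for a baseline evaluation (Visit 2), including clinical evaluation and mucosal specimen collection". Section 5.3.3 lists the Visit 3 assay as "Pre- and post-dose Immunoglobulin assay (~4 rectal sponges", and Section 5.3.2 has sponges collected before the enema and gel and again 30 minutes after the gel.

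The basic ANCOVA in 7.6 is specified as "regressing the continuous parameter at either post-Treatment 1 or post-Treatment 2 on the continuous baseline value and the categorical treatment group membership". It applies to all continuous measures, with no separate provision for the panel that has two pre-gel values. The plan runs every analysis with and without baseline adjustment, and prefers covariate adjustment to change scores for reasons of power.

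7.6 also says that longitudinal models with three or four time points will be investigated. It expects them to add little, because most parameters have only three time points.

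On stability, 7.6 reports for immunoglobulins that "intrasubject correlations are between 0.3 and 0.5 for various measures of IgA and IgG". For the listed cell phenotype measures it names parameters "which have intrasubject correlations of between 0.7 and 0.9". CCR5 parameters are put at around 0.5 and three cytokines at 0.7 to 0.8.

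**The concern.** With 12 participants per arm, 7.6 itself expects many parameters to differ between groups at baseline, and it adopts ANCOVA to deal with that. A covariate that correlates only 0.3 to 0.5 with the outcome removes little variance. This is the panel where a second pre-treatment reading is most useful, and the trial already collects and assays one. The reading precedes all study gel, so gel cannot have affected it and it is a legitimate covariate.

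The plan's reason for expecting little from longitudinal models, that most panels have three time points, does not apply to immunoglobulins, which have four. What is at stake is some precision in the comparison of each UC-781 arm with placebo on IgA and IgG. Naming the covariate in advance also settles which pre-gel value counts as baseline before any data are seen.

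**Working it through.** The protocol gives no effect size, SD or power for immunoglobulins, so there is no figure of its own to reproduce. Results below are in SD units.

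**Inputs**
- 12 per arm, 36 in total (Schema, Study Size).
- Intrasubject correlation ρ = 0.3 to 0.5 (Section 7.6).
- Level 0.05 (Section 7.6, the threshold for flagging a difference). Two-sided is assumed; the protocol does not say.
- Assumed: equal variance, and the same ρ between any two time points.

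**Formulas**
- Residual variance with one baseline: 1 − ρ².
- Residual variance with the mean of two pre-gel values: 1 − 2ρ²/(1 + ρ).
- Standard error of an arm difference: √(residual variance × 2/12).
- Power from the noncentral t with 36 − 3 − 1 = 32 degrees of freedom. This is the same for both models, since each has one covariate.

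**Example, ρ = 0.5.** One baseline: 1 − 0.25 = 0.750. Mean of two: 1 − 0.50/1.5 = 0.667. Ratio 0.667/0.750 = 0.889, a reduction of 11.1%. The standard error falls from 0.354 to 0.333 SD.

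| ρ | Residual variance, one baseline | Residual variance, mean of two | Further reduction | SE reduction | Power for 0.8 SD |
|---|---|---|---|---|---|
| 0.3 | 0.910 | 0.862 | 5.3% | 2.7% | 51.3% → 53.5% |
| 0.4 | 0.840 | 0.771 | 8.2% | 4.2% | 54.5% → 58.1% |
| 0.5 | 0.750 | 0.667 | 11.1% | 5.7% | 59.3% → 64.3% |

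In sample-size terms the gain is worth 12.7 to 13.5 participants per arm instead of 12. The difference detectable with 80% power falls from 1.125 to 1.095 SD at ρ = 0.3 and from 1.022 to 0.963 SD at ρ = 0.5.

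**Simulation check** (20,000 trials of 36 at each ρ; variance of the high-dose v placebo estimate)

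| ρ | One baseline | Mean of two | Both as separate covariates |
|---|---|---|---|
| 0.3 | 0.160 | 0.151 | 0.156 |
| 0.5 | 0.127 | 0.112 | 0.116 |

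The mean does better than two separate covariates under equal correlation, because it spends no extra degree of freedom.

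**Sensitivity for post-Treatment 1.** The Visit 2, Visit 3 pre-dose and Visit 5 sponges are all taken before the enema. The Visit 3 post-dose sponge is taken after enema and gel, so its correlation with the others may differ.
- Suppose it correlates 0.2 with each pre-gel sample and those correlate 0.4 with each other. One baseline leaves 1 − 0.04 = 0.960. The mean leaves 1 − 2 × 0.04/1.4 = 0.943. The reduction is 1.8%.
- Suppose instead that only the same-day correlation is 0.1 below ρ. With the mean as covariate the reduction is 0.7% at ρ = 0.3 and 2.7% at ρ = 0.5.

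**The case against.** The strongest reply is that nothing here is an error. ANCOVA on one pre-treatment value is valid and unbiased under randomization, 7.6 calls it the basic model, and combining two baselines for one panel is detail that an analysis plan could supply. The first two parts stand. The third stands only in part: 7.6 commits to a single baseline value and sets no exception, so this is a stated choice that can be bettered from data already in hand.

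The gain is also small. The panel is underpowered for 0.8 SD either way, and 7.6 plans stepdown corrections. At a level of 0.025, as for two arm comparisons, power moves only from about 39% to 42% at ρ = 0.3 and from 47% to 53% at ρ = 0.5. This stands. The plan does not claim good sensitivity for every panel, only for at least four of the six.

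Several stronger readings are tempting and are not supported:
- *The pre-dose sample goes unused.* It does not: the four-time-point longitudinal models could use it. The point is confined to the ANCOVA.
- *Same-day samples must correlate much more closely, so the loss is large.* No same-day correlation is given, and the two Visit 3 sponges differ by an enema and the gel. The gain could as well be smaller.
- *Visit 2 is the wrong baseline because 28 biopsies follow it.* Section 8.3 says biopsies heal within 3 days, Visit 3 comes 1 to 3 weeks later, and nothing in the protocol shows that biopsies shift immunoglobulins.
- *A safety judgement is compromised.* Section 1.1 says these assays are secondary endpoints and not safety indices.

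**Conclusion.** The point holds as a minor improvement. The immunoglobulin ANCOVA conditions on one of two available pre-gel values. Using their mean would lower residual variance by 5% to 11% and raise power for a 0.8 SD difference by about 2 to 5 percentage points, the upper end being reached only at ρ = 0.5.

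This rests on the protocol's correlations holding equally between all time points, on equal variances, and on an unadjusted two-sided 0.05 level. For post-Treatment 1 the gain could fall below 2% if the sponge taken after enema and gel correlates less with the pre-gel samples. The ranking of immunoglobulins as least stable covers only panels with a stated correlation; none is given for sloughing, histopathology or calprotectin.

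A reader might extend the point to epithelial sloughing, which 7.6 also lists at four time points. The Visit 3 procedures list only a post-dose lavage, so the remedy does not carry over.

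**What to change.** In Section 7.6, under mucosal immunoglobulins, add one sentence: the ANCOVA covariate is the mean of the Visit 2 and Visit 3 pre-dose values, on the scale used for analysis, for both the post-Treatment 1 and post-Treatment 2 comparisons, with a missing pre-gel value handled by the multiple imputation in Section 7.10. Handling it that way avoids mixing covariates of different reliability within one model, which would follow from substituting Visit 2 alone for some participants.

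The cost is the sentence itself. No samples, assays or degrees of freedom are added. It should be settled before unblinding.
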